#### Data Collection

All the study data will be collected through an electronic case report form (eCRF). To facilitate the completion of the eCRF, a specific module has been created and integrated into the EHR of the participating centers. The information that the researchers include in the eCRF will be exported to an anonymized database (without identifying patient data to ensure data confidentiality) for further analysis of the study data. The researchers will be responsible for creating a system that relates the numbers of the EHR (containing the eCRF data) with the anonymized code in the database where the data are exported and for maintaining the list of identification codes.

### Instruments

The Barthel index will be used to assess physical dependence and loss of autonomy of patients at the point of patient reception and preparation. Health care professionals will score patients based on whether they did or did not require physical assistance to perform daily activities, ranging from 0 (patient is dependent in all assessed activities) to 100 (patient is independent to perform the reflected activities) [37,38].

The criteria of the *American Society of Anesthesiologists* (ASA) will be used to evaluate the anesthetic risk and identify the clinical outcomes in patients at the point of anesthesia consultation. It scores patient’s overall health to describe 6 different levels (level I describes a normal healthy patient, whereas level VI describes a declared brain-dead patient whose organs are being removed for donor purposes) [39]. Only low-risk (ASA I and ASA II) patients are a candidate for MAS. Eventually, ASA III patients could benefit from MAS, after undergoing evaluation on individual basis for the risk-benefit balance of the ambulatory care (ie, ASA III without decompensation in the last 3 months) [10].

The information about mobile app usability by the intervention group will be collected through a modified version of the self-assessed mobile-based *Computer System Usability Questionnaire* [40]. Four focus groups—with 6-8 participants each—will be organized to collect qualitative data about the utility perceived by health professionals as well as intervention group patients’ experience with the app.

Both research tools will provide very insightful information that will eventually lead to changes in the Listeo+ functionality or content. In the event an incident occurs involving the cancellation, suspension, or rescheduling of surgery, the consumption of hospital resources will be recorded (consumption of medications, hospital stay, consumption of laboratory tests, diagnostic imaging, etc).

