#### Inclusion Criteria

To participate in this study, participants should be autonomous or dependent on one or more caregivers to perform their preoperative preparation, with the necessary technological and connectivity resources (ie, to dispose a smartphone or tablet mobile device with an Android or iOS operating system with an internet connection and familiarity with mobile technologies).

Patients who are autonomous to perform their preoperative preparation and lack the technological requirements but have caregivers with the necessary technological and connectivity resources who can supervise their preoperative preparation may also be included in the study.

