#### Exclusion Criteria

Patients with two scheduled operations during the same clinical episode or time period will be excluded from the study. Nonautonomous patients, whose caregivers cannot be located when personal preoperative recommendations (Multimedia Appendix 2) are provided, and patients of the intervention group who have not downloaded and registered on Listeo+ will also be excluded. To avoid the loss of patients, a rescue procedure will be used with patients who, within 7-14 days, have not registered on the Listeo+ app. A telephone call will be made urging them to register on the Listeo+ app. If a patient has not registered within 72 hours (3 days) after the rescue call has been made, he or she will be excluded from the study.

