### Study Outcomes

#### Primary Outcomes

The primary outcome will be measured as the average percentage of patient compliance with preoperative recommendations (the number of recommendations met by surgical intervention). Compliance with type 2 recommendations will be checked at the point of anesthesia consultation, whereas types 1 and 3 at the point of patient reception and preparation the day of surgery.

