### Sample Size and Statistical Plan

The sample size required to estimate the main objective of this study was calculated as 395 patients per group for a total of 790 patients. This estimate was made assuming an alpha risk of .05, a beta risk of .2, and a difference in proportions between the groups of 10%. The analysis will be performed considering per intention-to-treat (ITT) and per protocol populations. The ITT population will include all randomized patients, whereas the per protocol population will include randomized patients who finally obtain an appointment to undergo MAS.

In addition, statistical analyses will be performed using the R software version 3.3.2 (R Foundation for Statistical Computing). For all analyses, an alpha risk of .05 will be assumed; therefore, to consider a statistically significant difference, the *P* value of the contrast statistic should be ≤.05. The statistical analysis planned *a priori* will consist of a descriptive analysis of the demographic and clinical characteristics of patients. For quantitative variables, the mean, SD, 95% CIs, variance, SE, 5% trimmed mean, median, minimum, and maximum will be calculated. For qualitative variables, frequency distributions with their respective percentages will be calculated. To determine whether there are differences in the level of compliance with surgical recommendations between the group with written recommendations and the group with written recommendations plus the app, Fisher's exact test will be performed.

To assess the influence of sociodemographic and clinical characteristics of patients in the level of compliance with preoperative recommendations, multivariate logistic regression will be performed. Furthermore, the reasons for the exclusion of the ITT population will be included.

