### Allocation

Patients who meet the inclusion criteria and sign informed consent will be provided with an information sheet about the project and evaluated before participating in the study. To allocate patients to study groups, simple randomization 1:1 procedure will be used. To include patients in the study, each center will be provided with one randomization scheme generated by computer. Given the characteristics of the study, it is not possible to blind patients and professionals. Subsequently, we will collect sociodemographic data (age, sex, area of residence of patients, level of education of patients or caregivers using the app or patient or caregiver of the control group, occupation, marital status, and knowledge or handling of apps), clinical data (type of surgery, medical diagnosis [International Classification of Diseases, Ninth Revision], anesthetic evaluation, and medications taken), and functional situation by measuring disability (Barthel index).

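### The Barthel index is scored only on the day of surgery, by unblinded staff at the compliance check, so it is not a true baseline characteristic and is missing for patients who never reach reception

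*Protocol article*

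**What the plan says.** On timing, the Instruments section has this sentence: "The Barthel index will be used to assess physical dependence and loss of autonomy of patients at the point of patient reception and preparation". It makes clinical staff the scorers, who go by how much physical help a patient needs.

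When that contact takes place, from Primary Outcomes: compliance is checked for "types 1 and 3 at the point of patient reception and preparation the day of surgery". Type 2 recommendations are checked earlier, at the anesthesia consultation.

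Blinding, from Allocation: "it is not possible to blind patients and professionals". That section also lists the Barthel index, as the measure of functional situation, next to the sociodemographic and clinical data that are gathered once patients have been allocated.

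Analysis, from Sample Size and Statistical Plan: the two groups' compliance is compared with Fisher's exact test. Separately, a multivariate logistic regression is planned: "To assess the influence of sociodemographic and clinical characteristics of patients in the level of compliance with preoperative recommendations". The intention-to-treat population is everyone randomised.

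Autonomy also appears in the entry rules. Inclusion Criteria: "participants should be autonomous or dependent on one or more caregivers to perform their preoperative preparation". Exclusion Criteria rules out a group whose description begins "Nonautonomous patients, whose caregivers cannot be located when personal preoperative recommendations". Neither section mentions Barthel.

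**The concern.** A characteristic used to explain an outcome, or to show that randomised groups are alike, should be measured before allocation, in everyone, and independently of arm and outcome. As scheduled, the Barthel score does not meet these conditions.

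- **Time point.** It follows the whole app period. The rescue steps for patients who have not registered (7 to 14 days, then 72 hours) show that this period can exceed two weeks. Function can change in that time, for instance in traumatology patients.
- **Independence.** The scorer may know the arm and may just have seen how well the patient prepared.
- **Completeness.** Patients cancelled before the day, and no-shows, have no score. The Introduction links poor preparation to both, and cancellation is a secondary outcome that the app is expected to reduce. Whether the score is available could therefore depend on arm and outcome.

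At stake are the functional-status term in the regression, if there is one, and the description of the groups. The main between-arm comparison is not at stake.

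**Working it through.** **1. Order of events, section by section**

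| Step | Source in the protocol article |
|---|---|
| Consent signed before allocation | Ethical Aspects |
| 1:1 allocation, no blinding | Allocation |
| Recommendations given, app used, rescue call at 7 to 14 days, exclusion after a further 72 hours | Exclusion Criteria, Intervention |
| ASA class and type 2 compliance at anesthesia consultation | Instruments, Primary Outcomes |
| Barthel score **and** types 1 and 3 compliance at reception on the day of surgery | Instruments, Primary Outcomes |

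On the rescue timings alone, a patient can still be registering 14 + 3 = 17 days into the process. The ASA entry shows that a time point was chosen for each instrument, so the surgery-day Barthel is something the text fixes, not a detail left open.

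**2. Is Barthel in the regression?**

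Allocation groups it with the patient descriptors, but as a third item after the sociodemographic and the clinical lists. The statistical plan names only those first two classes. Its use as a covariate is therefore a reasonable inference and not a stated fact.

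**3. How many scores could be missing?**

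Inputs: N = 790 (Sample Size and Statistical Plan); cancellation rate about 4% (Introduction).

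- Expected cancellations: 0.04 × 790 = 31.6, about 32, or 0.04 × 395 = 15.8 per arm.
- The share cancelled before reception is not given, so cancellations contribute between 0 and about 32 missing scores. A patient cancelled at or after reception can still be scored.
- No-shows would add to this; their number is not given.
- The Introduction attributes 27% of cancellations to poor compliance: 0.27 × 31.6 = about 8.5 patients over both arms.

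**4. Does this matter for power?**

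First, the plan's own figure. With two-sided alpha 0.05, power 0.80 and a 10-point difference, maximum variance gives n = 2 × 0.25 × (1.960 + 0.842)² / 0.10² = about 392 per group. The pooled-variance formula gives 388 for 40% v 50%, 392 for 45% v 55% and 388 for 50% v 60%. The stated 395 is reproduced to within 3%; the base rate is an assumption, because the article gives none.

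Power for a comparison restricted to patients with a score:

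| Missing (assumed) | Patients of 790 | Power, 45% v 55% | Power, 50% v 60% |
|---|---|---|---|
| 0% | 0 | 0.804 | 0.808 |
| 4% | 32 | 0.788 | 0.792 |
| 10% | 79 | 0.761 | 0.765 |
| 20% | 158 | 0.711 | 0.716 |

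At the quoted 4% the loss is under 0.02 even if every cancellation came before reception. The issue is selective missingness and the quality of the score, not power.

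**5. Would an earlier score bring the missing patients back into the regression?**

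Only in part. Patients who never reach reception also lack types 1 and 3 compliance. For those who attended the anesthesia consultation, type 2 compliance can be known, and cancellation status can be known too. An earlier score would let them be described and included in analyses of those items. It would not complete their compliance percentage.

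**The case against.** A reader might infer that the protocol contradicts itself by deciding eligibility on autonomy and measuring autonomy only weeks later. The text does not support that. Eligibility concerns being able to carry out the preoperative preparation, whereas Barthel concerns physical help with daily activities. A patient can be independent in one and not in the other. No section makes Barthel the entry tool. Dependent patients with a reachable caregiver may enter, and candidates are evaluated before they take part.

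Further points on the other side, and what stands of each:

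- **The covariate role is not stated.** Correct. The point is conditional on that use or on use as a baseline descriptor.
- **The same patients lack outcome data.** Correct for types 1 and 3 compliance, so the missing score cannot be blamed for all of their loss.
- **A reminder app has no evident way to change physical dependence.** This stands, and it limits the bias. It does not answer the concern about arm-aware scoring at the compliance check, although that influence is a possibility and has not been demonstrated.
- **A score close to surgery describes the patient who carried out the preparation.** This is a fair reason to keep a surgery-day score as description, but not as the only one.
- **Fisher's exact test does not use Barthel.** Correct. The trial's main comparison of compliance does not depend on it.

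**Conclusion.** The point holds in a limited form. Instruments read with Primary Outcomes makes the only described Barthel score a post-randomisation one, taken by unblinded staff alongside the check of part of the primary outcome, and unavailable for randomised patients who do not reach reception. Cancellations account for at most about 32 of 790 such patients, and possibly none; no-shows are uncounted.

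This rests on two assumptions: that the score is meant as a patient characteristic in the regression or the group description, and that the background cancellation rate of about 4% applies to this trial. The conclusion does not extend to eligibility or to the Fisher's exact comparison. It is an inexpensive improvement to a supporting analysis and to the baseline description, not a threat to the main result.

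**What to change.** For patients still to be enrolled, score Barthel at the consent visit, before allocation, and use that score as the functional covariate and baseline descriptor. The consent visit suits this better than the anesthesia consultation, because ophthalmology patients under topical anesthesia do not attend the latter (Participants).

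Treat any surgery-day score, including the scores of patients already enrolled, as descriptive only, and report by arm how many are missing. State in the statistical plan whether functional status enters the logistic regression.

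The cost is a few extra minutes at the consent visit and one moved eCRF field. The article does not describe staffing at that visit, so the sites should confirm that the time is available. Recruitment is already under way, so pre-allocation scores will exist for only part of the sample, and the report should say so.

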### Data Monitoring and Validation

Electronic monitoring of the completion of the eCRFs will be performed to detect missing information and possible data inconsistencies, thus, ensuring their quality. For this purpose, the researchers will be contacted during the patient recruitment phase, 3 and 6 months after the start of the project, using confidential information access codes. The inclusion of patients according to the established criteria (inclusion or exclusion criteria), the correct completion of the eCRFs, the signing and filing of the informed consent form of participating patients, and any other aspects required by the research team will be reviewed. The monitor will communicate to the corresponding research team the variables that must be reviewed in cases of lost or inconsistent data.

### Technological Development, Integration, and Interoperability

To ensure proper communication between mHealth app users (patients and health professionals), a process of integration of information systems and interoperability between Listeo+ and EHR has been developed. This process was planned in 4 phases: (1) codesign of the system and pilot; (2) integration and technical tests; (3) simulation and pilot testing; and (4) real environment testing.

### Ethical Aspects of the Study, Confidentiality, and Privacy

The study protocol has been evaluated and approved by the Regional Ethics Committee of Andalusia through the Biomedical Research Ethics Portal of Andalucía (PEIBA, for its acronym in Spanish). This study will be conducted in accordance with the principles of the latest version of the Declaration of Helsinki and will follow the Good Clinical Practice guidelines of Spain.

Written informed consent duly signed by all patients, legal representatives, or caregivers participating in this study will be collected before patient allocation to study groups. Data confidentiality will be protected under the Spanish law that ensures the protection of personal data (Organic Law on Protection of Personal Data, 15/1999, December 13). The researcher of each center will be responsible for keeping a study file containing patient identification and information, including the informed consent form signed by patients. Throughout the study, all related documents will be located in a secure area of the participating center. Any analysis derived from the study will be performed from an anonymized database; it will not contain any identification of patients or caregivers but only a numeric code, through which it will not be possible to reveal their identities. At the end of the study, the researcher will be responsible for preserving the necessary documentation for at least 5 years.

## Results

Currently, this study is in the recruitment phase, which will end once 790 patients are included (395 for each arm). The data collection and cleaning phases are estimated to be completed in April 2019, and the analysis with the final results will be conducted in July 2019.

Previously, the technical aspects of interoperability between the hospital and the Listeo+ app backend (set of system components accessible only to the developers or platform administrators) were resolved successfully, defining an application programming interface for Web services. In December 2016, an eCRF was created that was fully integrated into the EHR of the participating centers.

Prior to the recruitment of patients, a pilot phase was conducted in January 2017 with the aim of identifying complications in the subsequent phases of recruitment and data analysis. During the pilot phase, face-to-face sessions were held in the hospitals with both health professionals and specialized information and communication technologies personnel. In these sessions, test runs were performed with several patients, verifying the effective communication between the systems and the usability of the new functionality integrated into the EHR. As a result, a telephone call was included in the protocol, at 7 and 14 days after the provision of recommendations during the anesthesiologist appointment, for the patients of the intervention group who had not downloaded their personal preoperative recommendations using the QR code. In addition, two new recommendations were added (see Multimedia Appendix 2: R1_18 and R3_24), and the wording of the recommendations was modified to facilitate patient understanding. Simultaneously, improvements were made in the design and functionality of Listeo+.

## Discussion

### Principal Findings

The introduction of new multifunctional technologies allows achieving different objectives in patient preparation, providing personalized information, and establishing an effective communication channel that facilitates patient monitoring by health professionals [30]. The evaluation of initiatives based on new technologies in the health sector is a fundamental element because of its subsequent adoption by the different stakeholders (patients, health professionals, and decision makers). According to the World Health Organization (WHO), the lack of evidence on the effectiveness and economic impact of mHealth-based interventions is one of the most important barriers for implementing these programs within the framework of the European Union [41]. In this sense, it is necessary to perform initiatives aimed at generating evidence on the effect of compliance with preoperative recommendations and their economic impact in MAS using mHealth apps, which evaluate their utility and efficiency in critical areas such as surgical patient safety. Taking into account the increasingly important role of citizens and patients in health systems, the possibility of having information about user experience (perceived usability and utility) makes it possible to evaluate the suitability of these tools in a real clinical setting.

### Relevance of the Study

Improvements in systems integration and interoperability could have great relevance. Currently, it has been possible to incorporate into the EHR of the participating centers a generator of preoperative recommendation lists that allows selecting the information according to individual patient characteristics. In addition, the structure of information systems for data exchange has been modified from the users’ mobile device using Listeo+ and the EHR in these centers. The learning process and the improvement in systems integration and interoperability can be used for other initiatives within the framework of mHealth apps in Andalusia, a region with a favorable environment for the development of initiatives based on new technologies and, by extension, to the rest of the NHS.

Furthermore, the interest of the study lies in the increase in MAS and the adoption of mobile devices and acceptance of mHealth apps by the population. Thus, the number of MAS operations in developed countries has continued to increase in recent years. In 2015, in Spain, 1,632,824 MAS operations were performed, corresponding to an increase of 4.2% from the period of 2010-2015 [11]. In addition, it highlights that the penetration level of smartphones is also increasing, even among the elderly, reducing the generation gap [42]. Finally, data from a local survey on the use of mHealth apps show that 73.8% of patients would use them if recommended by their doctor, which suggests a high level of acceptance of mHealth apps by the population [43].

